## Abstract

**Background:**

Donor site wounds after split-skin grafting are rather 'standard' wounds. At present, lots of dressings and topical agents for donor site wounds are commercially available. This causes large variation in the local care of these wounds, while the optimum 'standard' dressing for local wound care is unclear. This protocol describes a trial in which we investigate the effectiveness of various treatment options for these donor site wounds.

**Methods:**

A 14-center, six-armed randomized clinical trial is being carried out in the Netherlands. An a-priori power analysis and an anticipated dropout rate of 15% indicates that 50 patients per group are necessary, totaling 300 patients, to be able to detect a 25% quicker mean time to complete wound healing. Randomization has been computerized to ensure allocation concealment. Adult patients who need a split-skin grafting operation for any reason, leaving a donor site wound of at least 10 cm^2 ^are included and receive one of the following dressings: hydrocolloid, alginate, film, hydrofiber, silicone dressing, or paraffin gauze. No combinations of products from other intervention groups in this trial are allowed. Optimum application and changes of these dressings are pursued according to the protocol as supplied by the dressing manufacturers. Primary outcomes are days to complete wound healing and pain (using a Visual Analogue Scale). Secondary outcomes are adverse effects, scarring, patient satisfaction, and costs. Outcome assessors unaware of the treatment allocation will assess whether or not an outcome has occurred. Results will be analyzed according to the intention to treat principle. The first patient was randomized October 1, 2009.

**Discussion:**

This study will provide comprehensive data on the effectiveness of different treatment options for donor site wounds. The dressing(s) that will prevail in effectiveness, satisfaction and costs will be promoted among clinicians dealing with such patients. Thus, we aim to contribute a well-designed trial, relevant to all clinicians involved in the care for donor site wounds, which will help enhance uniformity and quality of care for these patients.

**Trial registration:**

http://www.trialregister.nl, NTR1849. Date registered: June 9, 2009

## Background

Split skin grafting (SSG) is a widely used reconstructive technique to repair skin defects (e.g. burns, chronic, and traumatic wounds) [1,2], including those that cannot be covered by a skin flap or are not likely to heal by secondary intention [3]. The wound created after harvesting the skin is called the donor site wound (DSW). Depending on the thickness of the SSG, the DSW should re-epithelialize completely in 7 to 21 days [3]. Optimum local care for these DSWs should promote wound healing and be cost-effective, while it should prevent complications, such as pain, discomfort, infection, and scarring. Particularly pain and discomfort are reported to occur more frequently from DSWs than at the recipient site [3-5].

Clinical practice shows a large number of dressings and topical agents for DSWs, while the optimum dressing choice for local wound care is unclear [1,2,6,7]. Consequently, large variation exists among health care professionals regarding their choice for wound dressing materials or topical agents to treat DSWs [8-10]. Based on national surveys, alginates appear to be the most commonly used primary dressing [8-10], probably due to their additional haemostatic properties [11,12]. They are followed by films, hydrofibers, silicone dressings and paraffin gauzes [8].

Available evidence comprises four systematic reviews (SRs), presenting a lack of strong evidence for the effectiveness of the different dressings for the treatment of DSWs, especially for alginates [1,2,6,7]. These SRs tentatively conclude that moist dressings are preferable over non-moist dressings in terms of wound healing. Hydrocolloid and films seem better than nearly all other materials (e.g. alginates, paraffin gauzes, hydrofibers, and foams) as to healing and pain [7]. Hydrofibers in turn seem to outperform tulle dressings in terms of wound healing and pain [13,14]. Although tulle dressings seem to be least suitable for the local treatment of DSWs, recent evidence shows that gauze-based dressings still have a place in wound care [15]. Some centers still adhere, or have returned to, these gauze-based dressings [16]. Silicone-based dressings have the advantage of being non-adhesive, although they tend to dislocate easily and do not seem to outperform alginates [17]. These conclusions are formulated cautiously as most authors state that more well designed and rigorous studies are needed.

We therefore conceived a trial to compare the six most promising dressing groups, based on common usage and available evidence. In this paper we will report on the design of our 14-center six-armed randomized clinical trial (RCT). This trial received the acronym "Rembrandt" trial, which stands for Recognizing Effective Materials By Randomizing & Assessing New Donorsite Treatments. In this trial we aim to answer the following question: Which of the following dressing materials for DSW of SSGs stand out in effectiveness: hydrocolloids, alginates, films, hydrofibers, silicone dressings, or paraffin gauzes, in terms of wound healing, adverse effects (e.g. pain and scarring), and costs?

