#### Surgical procedure

A SSG operation is to be performed with an electric or pneumatic dermatome or free hand-knife, according to local best practice. The SSG should preferably be between 0.20 and 0.30 mm to achieve a reasonably uniform depth of the DSW and should be taken from thighs, arms or buttocks. Method of hemostasis of the DSW is at the discretion of the surgeon (e.g. adrenaline-soaked gauze). However, the decision to use hemostasis must be made before randomization and will be recorded.

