### Randomization

Patients are to be randomized in the operation theatre, just after the skin harvest and hemostasis, and before the DSW is to be dressed. In each contributing center an appointed officer performs the randomization using an online computer software program (ALEA NKI-AVL, Amsterdam, The Netherlands, Release: 2.2.) to ensure allocation concealment. The trial is stratified by center, with a balanced allocation ratio for each treatment arm using a biased coin [22]. The biased coin method preserves most of the unpredictability associated with simple randomization [22].

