### Data analysis

Data coding and analysis will be carried out using SPSS software (PASW statistics version 18.0, IBM, Armonk, NY, USA). Differences in outcome variables will be analyzed on an intention-to-treat basis. A general linear model will be used to analyze the differences between the treatment arms for the various endpoints measured repeatedly, as the data are likely to be unequally distributed. Differences in wound healing time between the dressing groups will be examined using the Kaplan-Meier method and the Mantel-Cox log-rank test. Data analysis will be conducted by the authors and replicated by the Clinical Research Unit of the coordinating hospital. We will record any crossovers and make sure the patient returns to the initially allotted dressing. Missing data are dealt with by using the Generalized Estimating Equations model in our statistical analysis.

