## Discussion

In current clinical practice, a 'standard' wound such as a DSW does not appear to be associated with a uniform dressing choice [8]. Also the systematic reviews of available literature report a large clinical heterogeneity among the available trials [1,2,6,7]. To date, available evidence allows the tentative conclusion that dressings creating a moist environment seem to be preferable over gauze-based dressings in the management of DSWs. This recommendation is tentatively formulated because strong recommendations for clinical practice are hard to draw, mainly due to the poor quality and small sample sizes of the available trials. Therefore, most systematic reviews recommend new and large randomized clinical trials [2,6,7].

However, doing research in the realm of wound care involves much more than simply comparing wound care products in eligible patients. It poses many methodological and practical challenges in the design and execution of trials [24].

The first challenge is the design of our, intentionally pragmatic, RCT. To enhance the applicability and generalizability of the results of this trial, we chose a multicenter trial design and recruited patients from low- and high-volume centers like teaching hospitals and burns centers. We realize that for many surgical procedures, patients have better outcomes in high-volume centers [25-29]. However, split-skin grafting is a rather common procedure, also in smaller hospitals. Second, we are forbearing regarding local clinical care, for example by allowing several brands within each dressing group, different depths of skin grafting, and different methods of hemostasis. This helps mimicking 'real life', at the cost of losing some contrast between the six treatment arms.

Although we are liberal and pragmatic at some points, we feel we need to and can be strict in others. We urge the contributing centers to adhere to the same dressing type until complete wound healing is reached. This allows us to appreciate the true effects of each of the dressing types studied. Some argue this is not reflecting common practice [30], in which the dressing type is changed in response to any change in the clinical condition of the wound during the healing process. We do not think this will be a frequently occurring issue since these superficial DSWs usually have fairly short healing times. The protocol does allow for an antiseptic agent to be added in case of an (impending) wound infection.

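### The primary healing test is an unadjusted log-rank that ignores center and graft thickness: it is valid, but it gives up efficiency that could be recovered cheaply

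*Protocol article*

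**What the plan says.** All places are in the protocol article.

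- **Data analysis** names the test: "Differences in wound healing time between the dressing groups will be examined using the Kaplan-Meier method and the Mantel-Cox log-rank test". No covariate and no stratification factor is attached to it.
- **Randomization** stratifies by center only. On timing it says: "Patients are to be randomized in the operation theatre, just after the skin harvest and hemostasis, and before the DSW is to be dressed".
- **Background** ties healing time to thickness: "Depending on the thickness of the SSG, the DSW should re-epithelialize completely in 7 to 21 days".
- **Surgical procedure** narrows thickness, but as a preference: "The SSG should preferably be between 0.20 and 0.30 mm to achieve a reasonably uniform depth of the DSW". Powered dermatomes and a free hand-knife are both allowed. On hemostasis, "the decision to use hemostasis must be made before randomization and will be recorded".
- **Discussion** lists among the deliberate freedoms "different depths of skin grafting, and different methods of hemostasis", together with several brands per dressing group, and accepts some loss of contrast between arms in return.
- **Sample size** uses a one-way analysis of variance without covariates: 25% quicker mean healing, SD 3 days, 5% significance, 90% power, 15% dropout, 50 per arm.

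The article does not say that thickness is recorded, and it does not say that hemostasis, wound area or age affects healing time.

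**The concern.** The article names one patient-level factor on which healing time depends, lets it vary, and then fixes a primary test that leaves that variation as noise. Thickness is settled at harvest, before allocation, so adjusting for it is adjustment for a true baseline variable and opens no route to post-randomization bias. Center is also left out of the test, although allocation was balanced within it.

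For a log-rank test the price can exceed what the ANOVA-based sizing suggests, because omitting a prognostic factor pulls the marginal hazard ratio toward 1. At stake is the power to separate six dressings with about 50 patients each, in a trial whose authors already concede some loss of contrast.

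**Working it through.** **1. The plan's own figure.** 50 per arm less 15% leaves 42.5 evaluable; conversely 42 / 0.85 = 49.4, rounded up to 50. The article gives a 25% reduction but no reference mean in days and no pattern of arm means, so 50 cannot be reproduced uniquely. Take two extreme arms a distance d apart and four arms midway (assumption). The squared deviations sum to 2(d/2)² = d²/2, so the noncentrality is

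λ = n · (d²/2) / SD².

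With n = 42, SD = 3 and d = 2.687 days: λ = 42 × 3.610 / 9 = 16.85. Against the 5% critical value F(5, 246) = 2.251, power is 90.0%. So 50 per arm fits a mean of about 2.687 / 0.25 = 10.7 days. It fits equally with one arm differing by 2.08 days, a mean of about 8.3 days. Both means lie within the 7 to 21 days in Background.

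**2. Effect of adjustment on that scale.** If baseline covariates explain a share R2 of the variance, the residual SD is 3·√(1 − R2) and λ is divided by (1 − R2). R2 is assumed; the article gives none.

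| d (25% of mean) | R2 = 0 | 0.10 | 0.20 | 0.30 |
|---|---|---|---|---|
| 2.0 days (mean 8) | 63.1% | 68.5% | 74.4% | 80.7% |
| 2.687 days (mean 10.7) | 90.0% | 93.1% | 95.8% | 97.9% |
| 3.5 days (mean 14) | 99.3% | 99.7% | 99.9% | >99.9% |

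Simulated ANCOVA with 42 per arm and one arm differing by 2.08 days agreed with the middle row: 94%, 96% and 98% adjusted, against about 90% unadjusted.

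**3. Is that R2 range plausible?** A uniform spread over 7 to 21 days has SD 14/√12 = 4.0 days, above the planned total SD of 3, so the sizing did not assume the full span. If the thicknesses actually used moved healing over a quarter of it (3.5 days, uniform), R2 = (3.5²/12)/9 = 0.11; over a third (4.67 days), R2 = (4.67²/12)/9 = 0.20. These fractions are assumptions.

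**4. Effect on the log-rank scale.** Simulation with proportional hazards, no censoring, 42 per arm, one arm with a conditional hazard ratio of about 2.1, and 2000 runs:

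| R2 | Unadjusted log-rank | Log-rank stratified by thickness tertile |
|---|---|---|
| 0 | 94% | 94% |
| 0.10 | 86% | 93% |
| 0.20 | 78% | 92% |
| 0.30 | 68% | 91% |

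Type I error stayed at about 5 to 7% for the unadjusted test and 5 to 6% for the stratified one.

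**5. What can go wrong.**

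- *Useless covariates.* With two covariates and R2 = 0, λ shrinks by a factor of about (1 − 2/255), and power falls from 90.0% to 89.7%.
- *Wrong model.* When thickness acted additively on days, so that hazards were not proportional, the ordinary model-based Cox test had a type I error of about 8 to 13% at R2 of 0.10 to 0.50, against about 6 to 7% for the log-rank (1500 runs). ANCOVA on days stayed near 5%. Robust-variance Cox and accelerated failure time models were not simulated, and the stratified log-rank was checked only under proportional hazards.
- *Thin strata.* 300 / 14 = 21 patients per center, or 21.4 / 6 = 3.6 per arm within a center. Crossing center with three thickness classes would leave about 21.4 / 3 = 7 patients per stratum for six arms.

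**The case against.** The strongest reply is that nothing here is wrong. A log-rank test without covariates is valid under randomization, its error rate already allows for chance imbalance, and an article that summarizes a fuller protocol may leave covariate lists to that document. Validity stands in full. The last point stands only in part: the article names the primary test, and that test as named uses neither the randomization stratum nor the factor it calls decisive. If the full protocol adjusts, the article's sentence should say so.

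Several stronger readings are tempting, and the article does not support them:

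- *Thickness moves healing threefold in this trial.* The 7 to 21 days is a general statement about split-skin grafts. Here a range of 0.20 to 0.30 mm is preferred so that depth is reasonably uniform. Because it is only a preference, some variation remains, but its effect within the trial is unknown.
- *Hemostasis, wound area and age belong in the model too.* Only thickness is described as prognostic. Hemostasis is recorded before randomization, which makes it eligible, not useful. The 10 cm² minimum needs only a threshold check and does not show that area is measured.
- *Adjustment is free.* Recording of thickness is not stated, a free hand-knife has no dermatome setting, and the first patient was randomized on October 1, 2009. A complete-case adjusted analysis could therefore lose patients. A Cox model also yields a conditional hazard ratio and carries the error-rate risk shown above.
- *The conceded loss of contrast can be recovered.* Part of it comes from allowing several brands per group, which no baseline covariate addresses.
- *Power rises from 90% to 93, 96 and 98%.* That is one row of a table whose reference mean the article does not state.

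**Conclusion.** The point holds as a matter of efficiency. The stated healing test leaves out center and a pre-randomization factor that the protocol itself links to healing time. There is no bias and no invalid test.

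The gain is conditional. For assumed R2 of 0.10 to 0.30 on the ANOVA scale it is about 3 to 8 points if the planned difference is near 2.7 days, about 5 to 18 points if it is 2.0 days, and under one point if it is 3.5 days. The proportional-hazards simulation suggests a larger gain for the log-rank itself, about 7 to 23 points, but rests on one assumed hazard ratio and no censoring. If thickness varies little in practice, R2 is near zero and the change buys almost nothing, at a loss of about 0.3 points.

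These figures concern thickness; any gain from center was not quantified.

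**What to change.** **Analysis.** Make the primary healing analysis account for center and for prespecified graft thickness. One suitable form is a log-rank stratified by center, plus a prespecified accelerated failure time model or a Cox model with robust variance that contains arm, center and thickness category. State which of these is primary, and keep the unadjusted log-rank as a companion. Put thickness in the model and do not cross it with center as strata, given about 21 patients per center. Avoid relying on a model-based Cox test alone.

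**Data.** Record thickness for every patient as a category that can also be assigned to free hand-knife harvests, with a missing category so that no randomized patient is dropped. If the case record form already holds it, no new item is needed.

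**Other covariates.** Add hemostasis, wound area or age only if they are expected in advance to be prognostic, and name them before outcome data are examined.

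**Cost.** Analysis wording and at most one case record form item; no extra patients or visits. In exchange, the model gives a conditional effect estimate, some information is lost in small center strata, and about 0.3 power points go if the covariates prove useless.

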## Methods

### Protocol and registration

The methods applied in our 14-center RCT were specified in advance, documented in a protocol, and registered (http://www.trialregister.nl, NTR 1849). The study was approved by the local medical ethics committee and by the institutional review boards of each participating hospital or burns centre. The methods used are summarized here according to the revised CONSORT Statement [18].

### Design and setting

We designed a national, 14-center RCT with six treatment groups in the Netherlands (Figure 1). The coordinating center (Academic Medical Center at the University of Amsterdam) invited hospitals (i.e. departments of surgery, plastic surgery and otorhinolaryngology) and burns centers to participate in the trial, resulting in 13 contributing hospitals (4 university hospitals, 5 teaching clinics and 4 general hospitals) and 1 burns center.

**Figure 1 F1:**
[figure not shown]
**Flowchart of the Rembrandt Trial**.

### Eligibility criteria for patients

In this trial we include all adult patients, either hospitalized or under treatment in the outpatient clinic in one of the contributing hospitals or burns centre, who need a SSG-operation for any reason. The DSW should have a minimum size of 10 cm^2 ^(to allow proper application and investigation of the study dressings) and be suitable for all treatment options in the trial. Patients are included after full, understandable and neutral explanation by the treating physician or coordinating investigators and after giving written informed consent. Patients are excluded when they receive a treatment known to seriously impair normal wound healing (e.g. chemotherapy, corticosteroids, or local irradiation therapy) or if patients are not physically or mentally able to consent.

### Interventions

Before starting the trial, manufactures of the products involved were invited to develop a protocol how best to apply their wound materials for DSWs, to ensure correct and uniform application of the six different dressing groups:

1. A paraffin gauze-based material (e.g. Jelonet^®^, Adaptic^®^);

2. A hydrocolloid (e.g. DuoDERM^® ^E);

3. An alginate (e.g. Kaltostat^®^, Algisite^®^, Melgisorb^®^);

4. A semi-permeable film (e.g. Tegaderm^®^, Opsite^®^);

5. A silicone dressing (e.g. Mepitel^®^);

6. A hydrofiber (e.g. Aquacel^®^).

The coordinating investigators ([name] and [name]) or dressing manufactures orally instructed medical and nursing staff on the wards and out-patient clinics of the contributing centers at the beginning of the trial. Furthermore, they received written application advices as reminders for a uniform treatment protocol, e.g. regarding change frequency and treatment duration. Posters and pocket charts were also distributed to inform about inclusion criteria and contact persons.

#### Surgical procedure

A SSG operation is to be performed with an electric or pneumatic dermatome or free hand-knife, according to local best practice. The SSG should preferably be between 0.20 and 0.30 mm to achieve a reasonably uniform depth of the DSW and should be taken from thighs, arms or buttocks. Method of hemostasis of the DSW is at the discretion of the surgeon (e.g. adrenaline-soaked gauze). However, the decision to use hemostasis must be made before randomization and will be recorded.

#### Wound treatment

Local wound care according to the assigned dressing group starts directly after randomization (see heading Randomization). The brand of the dressing will be recorded. No combinations of products from other dressing groups in this trial are allowed to ensure that the effect found after completion of the trial can be attributed only to the dressing to which the patient was allocated. The optimum changing frequency will be pursued as advised for each dressing material. This may differ from no dressing changes (e.g. hydrofiber) to daily changes in case of leakage (e.g. hydrocolloid or paraffin gauze). We allow coverage of the primary dressings with cotton gauzes and bandages. The type of secondary dressings used will be recorded. Furthermore, we will record any crossovers and make sure the patient returns to the initially allotted dressing.

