### Study outcomes

#### Primary endpoints

The primary endpoint with respect to the effectiveness of wound dressings in the treatment of DSWs is time to complete wound healing. We define wound healing as re-epithelialization of the total wound surface. We decided this is not the case until all crusts have come off. This endpoint is to be assessed by an independent investigator who is not aware of the treatment given. The second primary outcome is pain from the donor site area. It is documented by the patient on a Visual Analogue Scale (VAS), varying from 0 (no pain) to 10 (intolerable pain). This is scored daily for the first two weeks postoperatively and twice a week during the third and fourth week, in a patient-held diary. Both primary endpoints are meaningful and relevant to patients and were therefore used for the sample size calculation [20].

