### Blinding

Blinding of patients and care-providers (e.g. doctors and nurses) is not possible because the treatment options cannot be masked. To overcome this possible source of performance bias, independent doctors and nurses of the outpatient clinic, who are unaware of the treatment allocation, will assess whether or not an endpoint has occurred [23].

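### Recorded healing dates may be interval-censored with a width that differs by arm, while Kaplan-Meier with log-rank takes them as exact

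*Protocol article*

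**What the plan says.** Under Wound treatment, the Protocol article makes change frequency a property of the product: "The optimum changing frequency will be pursued as advised for each dressing material". It then gives the range: "This may differ from no dressing changes (e.g. hydrofiber) to daily changes in case of leakage (e.g. hydrocolloid or paraffin gauze".

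Under Primary endpoints, the event needs sight of the whole wound: "We define wound healing as re-epithelialization of the total wound surface", with the added condition "We decided this is not the case until all crusts have come off". On who judges it: "This endpoint is to be assessed by an independent investigator who is not aware of the treatment given". The Blinding section states "Blinding of patients and care-providers (e.g. doctors and nurses) is not possible because the treatment options cannot be masked" and gives the endpoint assessment to outpatient-clinic doctors and nurses who do not know the allocation.

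Under Data analysis: "Differences in wound healing time between the dressing groups will be examined using the Kaplan-Meier method and the Mantel-Cox log-rank test". The same section mentions Generalized Estimating Equations, but for missing data, not for dating an event.

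The article states neither an inspection schedule shared by all arms nor a rule for dating healing that occurs between two inspections.

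**The concern.** Kaplan-Meier and the log-rank test take each recorded healing date as the true one. A wound that is looked at only now and then gives less: healing happened after the last look at which it was open and no later than the first look at which it was closed. If the gap between looks is the same in every arm, the delay is shared and largely cancels in the comparison. If the gap follows each product's change advice, the delay differs by randomized arm, and the arm looked at less often appears slower with no biological difference.

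Randomization and intention to treat do not remove such a difference, because it would come with the allocated dressing. More patients would only make it more likely to reach significance. At stake is which dressing is declared fastest, and the article's Discussion section in the abstract says the prevailing dressing will be promoted among clinicians.

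**Working it through.** **1. Can inspection depend on the arm?** Side by side, the sections give this chain:
- The assessor must see the total surface with crusts off (Primary endpoints).
- The assessor must not know the treatment, yet dressings cannot be masked (Blinding). A dressing in view would reveal the allocation, so the assessor has to see the wound undressed.
- How often the dressing comes off is set by product and may be not at all in one arm (Wound treatment).

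Frequent undressed inspection in all arms is hard to square with an arm that has no dressing changes. That inspection follows dressing change remains an inference.

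**2. Scale: the plan's own difference.** Inputs from Sample size: one-way ANOVA, alpha 5%, power 90%, SD 3 days, 50 per group, 15% dropout. Evaluable: 50 × 0.85 = 42.5, taken as 42. The reference mean is not given, so 50 cannot be strictly reproduced. With noncentrality λ = n·Σ(μᵢ − μ̄)²/SD²:
- Two extreme arms, four midway: Σ = δ²/2. At n = 42, power 90% needs δ = 2.69 days (λ = 42 × 2.69²/2/9 ≈ 16.9). As 25% of a mean, that is 2.69/0.25 ≈ 10.8 days. At an assumed mean of 11 days the required n is 41, or 49 with dropout, close to the stated 50.
- One deviating arm: Σ = 5δ²/6, δ = 2.08 days, a mean of 2.08/0.25 ≈ 8.3 days.

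The detectable difference is thus about 2.1 to 2.7 days. Over the 7 to 21 days in the Background, 25% is 1.75 to 5.25 days.

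**3. Recording delay.** With inspections every v days, the mean delay from healing to the next look is v/2. Against a daily arm the false difference is (v − 1)/2: 1.0 day for v = 3, 2.0 for v = 5, 3.0 for v = 7.

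**4. False rejection by the six-arm log-rank test.** Assumptions: identical normal healing times in all arms, SD 3, 42 per arm, no dropout censoring, healing recorded at the first look after it occurs. Two set-ups were simulated: A, mean 12 days, random start of the inspection grid, 500 runs; B, mean 10.7 days, grid fixed from day 0, 1,000 runs. Intervals and means are assumptions.

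| Inspection intervals (days) | A | B |
|---|---|---|
| all daily | 5.2% | 6.1% |
| all every 3 | 5.4% | – |
| all every 7 | 3.4% | – |
| five daily, one every 3 | 28% | 35% |
| five daily, one every 5 | 83% | 92% |
| five daily, one every 7 | 99% | >99% |
| two daily, four every 3 | 41% | – |

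Monte Carlo error in A is about √(0.05 × 0.95/500) ≈ 1 point near 5%. In two-arm comparisons (set-up A, 1,000 runs), a gap of 1 versus 2 days already gives 11.6%, and 1 versus 3 gives 32%. The excess comes from unequal intervals, not from interval censoring as such.

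**5. Interval-censored analysis.** A normal interval likelihood, with each patient contributing Φ((U − μ)/σ) − Φ((L − μ)/σ), where L is the last open and U the first healed look, was tested by likelihood ratio with no true difference.
- Set-up A, 400 runs: 5.5% (1 vs 3 days), 4.8% (1 vs 5), 8.3% (1 vs 7), 5.0% (six arms at 1,1,3,3,3,7, where log-rank gave 98%). Estimated differences were within 0.06 day of zero.
- Set-up B, 200 runs: 4.5% (1,1,1,1,1,7) and 5.5% (1,1,3,3,7,7).

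**The case against.** The strongest reply is that the link between inspection and dressing change is nowhere stated. The article condenses a fuller protocol, written application advice was distributed, and a standardized case record form exists. A visit schedule and a dating rule may sit there. An independent, unaware assessor in the outpatient clinic could point to a separate assessment, detached from the product routine. With a common interval the log-rank test is sound, as the table shows. All of this stands, and it is why the point is conditional.

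Three stronger readings are tempting and not supported:
- A reader might infer that the primary comparison is biased. That depends on an inspection schedule the article does not give.
- A reader might take none-to-daily as the routine contrast. Daily changes are named only in case of leakage, so this is the outer range. Five arms seen daily and one weekly is an illustration, not the described design.
- A reader might infer that the dressing stays in place, and the wound unseen, until healing, from "We urge the contributing centers to adhere to the same dressing type until complete wound healing is reached". That sentence concerns not switching dressing type. The Co-interventions section foresees care during dressing changes in all arms.

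A see-through dressing might also be read without removal. That would reveal the allocation to the assessor, and it would give that arm extra looks, so it does not restore equality.

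The remedy has limits too. It was checked with a correctly specified model and inspection times unrelated to healing, and one scenario came out above nominal (8.3%). Where an arm has no look before healing, the interval starts at day 0 and the result leans on the assumed distribution.

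What remains is not a missing visit table. The article names a right-censored method for an endpoint seen at discrete occasions, alongside change frequencies that differ by arm on purpose.

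**Conclusion.** The concern holds in conditional form. If inspection follows dressing change, healing dates are interval-censored with arm-dependent width, and the stated analysis is open to bias against arms inspected less often. Under assumed gaps of 3 to 7 days against daily, the false difference of 1 to 3 days is of the same order as the 2.1 to 2.7 days the trial can detect. These sizes rest on assumed intervals, an assumed mean (10.7 or 12 days), normal times with the plan's SD of 3 days, and 42 evaluable patients per arm. With equal intervals the problem disappears. The plan should be changed because the protection is cheap and little is lost if inspections prove equal. The stated sample size is not called into question here; it was used only for scale.

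**What to change.** - Record for each patient the date of the last inspection with the wound not healed (day 0 if none) and of the first inspection with it healed.
- Make the primary analysis of healing time interval-censored: an interval-censored log-rank test, or an accelerated failure time model with interval likelihood, accounting for center.
- Keep Kaplan-Meier with log-rank on first-seen-healed dates as a sensitivity analysis, and report inspection intervals by arm. If inspections are common to all arms, the two analyses should agree.
- State whether the assessment schedule is common to the arms. The investigators must reconcile how assessment fits with the per-product change advice; no dressing-change rule is proposed here.

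Cost: at most one extra date on the case record form (which is not shown and may already hold it), and analysis outside the SPSS Kaplan-Meier routine. The price in interpretation is reliance on the model's form in arms with few inspections before healing.
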